### Risks to participants

There are minimal risks to participants, namely breach of confidentiality/privacy and minimal blood loss obtained for the serum biosamples for the biomarker panel at each time point. Participants will have an arterial line placed as a SOC and biosamples will be obtained from this existing line. Thus, no additional pain, bruising, or bleeding due to an additional needlestick will occur when obtaining the biosamples. Blood is drawn frequently from arterial lines for clinical care and thus this study will not increase the risks associated with SOC testing. The study’s risks to participants are both minimal and consistent across the entirety of the planned study population.

### Adequacy of protection against risks

To lessen the probability and/or magnitude of risk of breach of confidentiality, the following procedures will be instituted: (1) in-person informed consent will be obtained in a private space without coercion, allowing adequate time for questions, (2) only IRB-approved consent forms will be used, (3) signed consent forms will be stored in a locked file cabinet separate from the study database with a restricted file linking participant identifiers with their corresponding study identification number, (4) clinical care will not be altered whether patients decide to participate or not, (5) participants can withdraw from the study at any time, (6) the study database will be de-identified, restricted, and password-protected, and (7) only the minimal amount of blood required will be collected. This study will abide by the institutions’ data security policy per our IRB.

### Vulnerability of study population

The study population includes primary, adult deceased donor OLT recipients at our institution. Children, pregnant women, lactating women, and prisoners will not be included in this study. Patients meeting inclusion criteria may be members of particular special populations, including institutional employees, adults unable to consent (e.g., inability to communicate due to critical illness or altered mental status), cognitively impaired individuals, those with impaired decision-making capacity, and/or individuals not able to understand English. Members of these special groups are not a specific focus of this study. Nonetheless, to optimize safety for these potential participants, the following protocol will be enforced: (1) employee status will not be collected as data, (2) only a legal surrogate will be able to give informed consent for study participation for those patients unable to consent, with cognitive impairment, or impaired decision-making capacity, (3) for those patients not able to clearly understand English, they will only be considered for enrollment if the informed consent process occurs in their primary language through an official interpreter, (4) all data will be de-identified and stored in a restricted database prior to analysis, and (5) participants will be withdrawn if they appear to be unduly distressed.

This research does not involve individuals who are vulnerable to coercion or undue influence. All patients who undergo liver transplantation at our institution undergo a rigorous, standardized, and formal review process for liver transplant candidacy prior to surgery. Vulnerable populations are not being targeted for enrollment in this study.

Gender, race, and ethnicity are plausible covariates in the research questions of this study and are planned for inclusion in data collection and analysis. Women and members of minority, non-white ethnic groups comprise approximately 35% and 30%, respectively, of all adult OLT cases performed annually [46, 47]. Prior data suggest women and racial or ethnic minority groups experience disparities with respect to access and outcomes in the perioperative OLT setting [46, 47]. Study team educational meetings and debriefings will occur to increase awareness of these disparities and promote equal access to study participation.

This study will employ JAMA definitions for “race” and/or “ethnicity,” in which (1) the source of classification is described (i.e., white, black, etc. as reported by the Emory Transplant Center and electronic medical record based on the US Office of Management and Budget’s Revisions to the Standards for the Classification of Federal Data on Race and Ethnicity), (2) reasons for assessment delineated (given known gender and ethnic disparities and the mandate by the NIH to report such data consistent with the Inclusion of Women, Minorities, and Children policy), and (3) race/ethnicity of the study population is reported in the results section of any manuscript. Racial and ethnic classifications of subjects will be used for descriptive statistics.

### Potential benefits of the research

Due to its observational design, participants will have no direct benefit through participation in this study. However, the information obtained from this study may serve as generalizable knowledge that advances the care of deceased donor OLT recipients in the future.

### Oversight and monitoring

The study steering committee will include the PI, PI’s mentors, and study coordinator. The PI and steering committee will monitor recruitment, enrollment, data collection and management, and oversee results reporting and publication. The committee will meet on a regular basis to oversee the study and ensure successful completion.

Given its observational design, this study is not deemed a clinical trial per current NIH guidelines and thus the appointment of a formal data monitoring committee is not required. Nonetheless, all potential adverse events will be recorded by the study team and reported to our IRB. The consent form describes how participants can report any concerns regarding participation in the study.

If an enrolled participant decides to withdraw from the study, their clinical data and biosamples will be removed from the study. This option is detailed in the consent. We do not anticipate circumstances under which participants will be withdrawn from the study without their consent.

## Discussion

### Association of hyperoxemia and EAD

We anticipate (1) increasing peri-reperfusion PaO_2_ is associated with EAD, (2) the odds of EAD increase when exposed to peri-reperfusion hyperoxemia compared to non-hyperoxemia, (3) PaO_2_ quartiles may have a differential effect on EAD, and (4) certain sub-populations may have higher odds of developing EAD when exposed to hyperoxemia. Such findings would lend evidence to an understanding of EAD as an inflammatory condition exacerbated by the re-introduction of excess oxygen. If validated, anesthesiologists can titrate FiO_2_ to a goal PaO_2_ to mitigate the impact of EAD and improve postoperative outcomes after OLT.

Nonetheless, our study protocol has a few limitations. As a pilot study, our protocol may be underpowered to detect a change. Alternatively, our study may not capture the key timeframe linked to the risk of EAD after oxygen re-exposure. It is possible oxygen exposure beyond the first 2.5 peri-reperfusion hours may be important for IRI and the development of EAD. Additionally, it is possible peri-reperfusion hyperoxemia confers increased risk only in a particular subgroup of patients undergoing OLT, e.g., recipients with metabolic dysfunction-associated steatohepatitis (MASH). While this pilot study will be insufficient to answer these questions, trends in data may serve to alter a subsequent larger study and address any of these findings.

### Association of immune dysregulation and EAD

We anticipate (1) distinct, perturbed cytokine, protein, and HIF-1α levels are associated with the development of EAD, (2) recipients who develop EAD have greater proinflammatory activity and/or less anti-inflammatory activity than those without EAD, and (3) peri-reperfusion hyperoxemia alters the pattern of expression of cytokine, protein, and HIF-1α levels. Such findings would lend evidence to an understanding of EAD as an inflammatory condition characterized by pathologic dysregulation of innate immune defenses with the re-introduction of oxygen. If validated, future studies could investigate the peri-reperfusion administration of immunomodulatory agents against specific perturbed cytokines, proteins, and/or HIF-1α to mitigate the impact of EAD and improve postoperative outcomes after OLT.

This aim also has limitations. As a pilot study, our protocol may be underpowered to detect a change. It is also possible there is no correlation between the tested peri-reperfusion biomarkers levels and EAD because the key biomarkers are not in the selected panel or biomarker levels are altered outside our studied timeframe. Given the inclusion of biomarkers linked to IRI in our panel, we plan to analyze the biomarker panel in the first 13 patients and if there is no signal, we plan to include a later time point of biosample collection.

Biomarker levels may be affected by the intraoperative and postoperative administration of immunosuppressive agents. At our institution, a dose of methylprednisolone is given intraoperatively during the neohepatic phase after hemostasis is achieved. Thereafter, a short course of methylprednisolone is initiated on the first postoperative night. Postoperatively, standing mycophenolate mofetil is started the evening of day zero and tacrolimus on day one or two depending on the patient’s baseline renal function. While these doses are relatively constant, another agent, basiliximab, is administered intraoperatively after methylprednisolone for patients with a creatinine clearance of < 60 mL/min to delay initiation of reduced-dose tacrolimus in an effort to reduce kidney injury [48]. The specific immunosuppressive agents and timing of administration will be recorded for each patient.

Our timepoints for serum biosample collection were chosen to minimize variability in immunosuppressant exposure. The first serum biosample is obtained prior to the administration of any immunosuppressive agents. The second serum biosample, obtained 2 hours after reperfusion, is most likely drawn after the administration of intraoperative methylprednisolone and possibly basiliximab depending on the degree of bleeding, resuscitation required, and baseline renal function. The third serum biosample, obtained 48 hours after reperfusion, will be drawn after methylprednisolone and mycophenolate mofetil exposure, and tacrolimus for most patients as well. We will explore if the administration and timing of immunosuppressive agents affects biomarker levels and may modify the patients captured to minimize variability if there is a signal.

Finally, our results may be impacted by large volume blood product resuscitation due to coagulopathy during OLT. Participant blood turnover with donated blood products may affect or “wash-out” our biomarker levels. This would most likely lead to low levels of all tested biomarkers at the second and third timepoints. If the first serum biosamples analyzed demonstrate this effect, we will consider altering the timepoints tested to focus on early events. Alternatively, if a specific biomarker showed statistically significant change over the course of the protocol despite high volume blood product resuscitation, it could provide unique insight into the immune dysregulation associated with EAD.

### Unique challenges assaying serum HIF-1α

Investigations of serum HIF-1 α have unique challenges because it is a transcription factor. Unlike extracellular cytokines, HIF is an intracellular heterodimeric transcription factor with one of three tightly regulated α subunits (HIF-1α, HIF-2α, and HIF-3α) that binds to an oxygen-dependent β subunit. During normoxia, cytoplasmic HIF-1α α-subunits are degraded by factor inhibiting HIF (FIH) and prolyl hydroxylase domain (PHD) enzymes via a von Hippel-Lindau polyubiquitination, protease-dependent pathway [49]. Conversely, during hypoxia, FIH and PHD are inhibited and HIF-1α levels increase, partly due to protein stabilization [50]. HIF-1α subsequently undergoes translocation from the cytoplasm into the nucleus where it induces the transcription of genes involved in cellular metabolism, glycolysis, angiogenesis, cytoskeletal formation, and hormonal regulation [50]. HIF-1α signaling can quickly reverse with normoxia [50].

HIF-1α has largely been studied in tissue via protein quantification with Western blotting or immunohistochemistry [50]. Immunohistochemistry studies are advantageous because they can identify the cellular location of HIF-1α, which aids in the interpretation of the role of this transcription factor in the disease process. Conversely, the Meso Scale Discovery total HIF-1α assay that will be employed in our protocol uses whole blood lysate electrochemiluminescence technology and a sandwich immunoassay, similar to ELISA. This method examines circulating HIF-1α levels, precluding intracellular location, with the presumption intracellular HIF-1α is released extracellularly into the blood after endothelial injury and cell death. This should occur in our study as IRI causes hepatocellular damage, sinusoidal endothelial injury, and cell death.

The extracellular release kinetics of HIF-1α following endothelial injury have been assessed in a rat model [51]. In this study, HIF-1α levels in cell-culture medium and plasma were measured via ELISA and the results were validated using Western blotting and immunohistochemistry. HIF-1α levels reached maximum concentrations approximately 2 hours post injury *in vitro* and 2 days post injury *in vivo* [51]. Clinically, elevated circulating levels of HIF-1α are linked to cellular injury in other disease processes in renal, cardiovascular, and cancer research [52–57].

Despite these challenges, it is valuable to examine HIF-1α because it is widely recognized as the universal regulator of the cellular response to hypoxia and interacts with inflammatory cytokines, many of which we are studying. The protective effects of ethyl 3,4-dihyroxybenzoate, a PHD inhibitor and anti-oxidant, demonstrated mitochondrial protection and mitigated hepatocellular necrosis in a partial liver IRI mouse model [58]. Additionally, HIF-1α upregulates HO-1, a cytoprotective molecule in IRI, and TNFα, a proinflammatory cytokine central to IRI, and cross-communicates with the NF-κB pathway [50]. HIF-1 α is thus a potential therapeutic target during OLT as hypoxemia and ischemia are hallmarks of IRI.

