### Procedures

This study was approved by the Emory University institutional review board (IRB), protocol number 5728. Study enrollment began on August 1, 2023. At the time of publication, this study has enrolled thirty-four patients and no data analysis has been performed. A serum lab protocol capturing PaO_2_ on serial arterial blood gas (ABG) analysis, other standard of care (SOC) tests, and cytokine, protein, and HIF-1α (biomarker) levels via serum biosample collection was implemented “Table 5.” Peri-reperfusion serial ABG will be obtained ~30 minutes before through ~2 hours after reperfusion within the SOC.

**Table 5 pone.0301281.t005:** Subject serum lab evaluation timeline.

Time Point	Serum Laboratory Values
Admission	CMP, CBC, INR, Fibrinogen (SOC)
After anesthesia induction	Biomarker Panel
Peri-reperfusion	Serial ABG (SOC)
~2 hours after reperfusion	Biomarker Panel
~48 hours after reperfusion	Biomarker Panel
Postoperative day 2	CMP (SOC)
Postoperative day 7	INR, Bilirubin, AST/ALT (SOC)
Postoperative days 1–7	Serial AST/ALT (SOC)

CMP indicates complete metabolic panel; CBC, complete blood count; INR, international normalized ratio; SOC, standard of care; ABG, arterial blood gas; AST, aspartate aminotransferase; ALT, alanine transaminase. *The study team will only collect biosamples for the biomarker panel*.

The study team will collect peripheral serum biosamples at planned intervals to test the biomarker panel. Biosamples will be obtained via an arterial line, placed preoperatively as a SOC procedure. All intraoperative serum biosamples will be obtained by the anesthesiologist. All postoperative serum biosamples will be drawn by the ICU or inpatient floor nurse. The other tests are SOC and will be obtained and analyzed in their usual fashion. Extra labs will be obtained at the discretion of the anesthesiologist or intensivist within the SOC.

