At each time point outlined for biosample collection, about 12 mL of blood will be collected into 2 edetic acid (EDTA) tubes (about 6 mL in each tube). Each subject will have 3 blood draws, about 36 mL of blood collected in total. Within 30 minutes of collection, serum biosamples will be processed via centrifugation at 4°C at 2,000g for 20 minutes to separate the plasma from the blood cells. The upper layer of plasma will be transferred via pipet to 1.5 mL cryovials. Upon centrifuging, every 4 mL of blood makes about 2 mL of centrifuged plasma. Thus, 12 mL of blood should make about 6 mL of centrifuged plasma, which will then be aliquoted to four 1.5 mL cryovials. A summary of serum biosample collection and processing is in “Table 6.” All tubes and cryovials will be labeled with the date and time of collection, protocol number, study identification number, and timepoint letter. Biosamples will be stored in a -80° freezer in the laboratory for later batch analysis. Standard kits to test these biomarkers, including Meso Scale Discovery Assay kits and multiplex ELISA, will be performed in duplicate in a laboratory per standardized manufacturer guidelines.

**Table 6 pone.0301281.t006:** Summary of serum biosample collection and processing.

Timepoint	Timepoint Letter	Patient Location	Source	Biosample and Tubes	Samples Stored
After Induction of General Anesthesia	A	OR	Peripheral Blood	~12 mL total (~6 mL in 2 purple top EDTA tubes)	4 cryovials of EDTA plasma (1.5 mL each)
2 Hours after Reperfusion	B	OR	Peripheral Blood	~12 mL total (~6 mL in 2 purple top EDTA tubes)	4 cryovials of EDTA plasma (1.5 mL each)
48 Hours after Reperfusion	C	ICU or Inpatient Floor	Peripheral Blood	~12 mL total (~6 mL in 2 purple top EDTA tubes)	4 cryovials of EDTA plasma (1.5 mL each)

EDTA indicates edetic acid.

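### The HIF-1α assay is described as using whole blood lysate, but all drawn blood is processed to EDTA plasma and nothing else is stored, so HIF-1α cannot be measured as described

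*Protocol article*

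**What the plan says.** Two parts of the protocol article describe the specimen for HIF-1α.

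- **Discussion, Unique challenges assaying serum HIF-1α.** The named commercial total HIF-1α assay, which the article says will be employed in this study, "uses whole blood lysate electrochemiluminescence technology and a sandwich immunoassay, similar to ELISA". The same paragraph then states what the result means: "This method examines circulating HIF-1α levels, precluding intracellular location". The presumption given is that intracellular HIF-1α escapes into the blood after endothelial injury and cell death.
- **Methods, Procedures.** At each time point about 12 mL is drawn into two EDTA tubes, and "serum biosamples will be processed via centrifugation at 4°C at 2,000g for 20 minutes to separate the plasma from the blood cells". Then: "The upper layer of plasma will be transferred via pipet to 1.5 mL cryovials". The yield is also given: "12 mL of blood should make about 6 mL of centrifuged plasma, which will then be aliquoted to four 1.5 mL cryovials". Table 6, in its column of stored samples, has the same entry for time points A, B and C: "4 cryovials of EDTA plasma (1.5 mL each" (closing bracket omitted). No whole-blood aliquot, retained cell fraction or lysis step is described.

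On timing, Procedures reports that "this study has enrolled thirty-four patients and no data analysis has been performed".

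**The concern.** The specimen decides two things: whether the assay can be run on what is in the freezer, and what the number means if it can.

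HIF-1α is named in the abstract, the hypothesis, Aim 2, the biomarker panel (Table 4) and the statistical analysis, and it has its own section in the Discussion. The article describes HIF as an intracellular transcription factor. Lysing whole blood would release whatever HIF-1α the blood cells hold, so a lysate value would mix that with any protein released by the injured graft. A plasma value fits the stated reading, but plasma is not the specimen that the assay is said to use.

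There is a practical consequence too. The Discussion plans to analyse the panel in the first 13 patients and to add a later sampling time if there is no signal. It would also take low levels of all markers at the second and third draws as a sign of transfusion wash-out. If the kit did not perform in plasma, which the documents leave open, low HIF-1α values could have a technical cause and be read as biology.

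**Working it through.** The point rests on setting the two descriptions side by side. The only arithmetic is a volume balance, which shows whether any whole blood is left over.

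**Inputs (Procedures and Table 6).** Two EDTA tubes of about 6 mL per draw; every 4 mL of blood gives about 2 mL of plasma; four cryovials of 1.5 mL per time point; three draws per patient.

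**Reproducing the article's figures, per draw**
- Blood drawn: 2 × 6 mL = 12 mL.
- Plasma obtained: 12 mL × (2/4) = 6 mL.
- Cryovial capacity: 4 × 1.5 mL = 6 mL, which equals the plasma obtained.
- Total over three draws: 3 × 12 mL = 36 mL, as stated.

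**Whole blood left for a lysate:** 12 mL drawn − 12 mL centrifuged = 0 mL at each time point.

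The figures close exactly. The described draw is fully used to make plasma, and the stored plasma fills the listed vials.

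**Each specimen against the article's statements**

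| If the specimen is | Assay as described (whole blood lysate) | Stored material (EDTA plasma) | Stated meaning (circulating, released extracellularly) |
|---|---|---|---|
| Whole blood lysate | agrees | conflicts | conflicts, because blood-cell HIF-1α is included |
| EDTA plasma | conflicts | agrees | agrees |

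Neither specimen satisfies all three, so at least one statement has to change.

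**How much of the study is involved**
- Panel: Table 4 lists IL-1β, TNFα, IL-2R, IP-10, MIG, IL-8, MCP-1, RANTES, PTX3, IFN-γ, IL-6, HO-1 and HIF-1α. That is 13 markers, of which one is affected.
- Patients already enrolled at publication: 34/40 = 85%, leaving 40 − 34 = 6. This count matters only if lysate turns out to be required.

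**The case against.** The strongest reply is that the lysate phrase is a loose description of a commercial kit and not a sampling instruction. It appears once, in the Discussion. No part of the Methods says that lysates will be prepared. The rest of the same section fits plasma: its heading speaks of serum, it refers to circulating levels, and the rat study it relies on measured HIF-1α in culture medium and plasma by ELISA. Procedures also says that the kits will be run to manufacturer guidelines, and a laboratory manual that is not shown may settle the matter. Details of assay validation may properly be left to such a manual.

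Much of this stands. The lysate wording may well be the mistake, and the absence of validation detail is not a fault in an article. Two stronger readings are therefore not supported:

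- **A reader might infer that HIF-1α is unmeasurable in this study.** The documents do not say whether the named kit accepts EDTA plasma, and they cite an animal study that measured HIF-1α in plasma.
- **A reader might infer that HIF-1α data are already lost for 34 of 40 patients, or for 34 × 3 = 102 of 40 × 3 = 120 planned samples.** This would follow only if lysate is required. The sample count also assumes that every enrolled patient completed all three draws, whereas the article reports enrolment and not sample completeness.

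Condensation does not explain the conflict itself. The article gives the tube type, volumes, spin settings and aliquots, and it separately gives the specimen for the assay that it says will be employed. Both are stated, and they disagree.

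**Conclusion.** The article contradicts itself on the HIF-1α specimen, and its description of the assay also conflicts with its own interpretation of the result. As written, HIF-1α cannot be measured as described. This is more than a slip of wording, because the specimen determines whether a named Aim 2 biomarker can be run and what its values represent.

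The reach is limited. One of 13 panel markers is affected. Aim 1, the primary outcome (EAD), the other 12 markers and the sample size, which is based on IL-8, are untouched.

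The conclusion assumes that Table 6 lists everything retained and that no additional whole-blood tube is taken. It assumes nothing about the kit's suitability for plasma, which only the manufacturer's documentation can settle. The timing also needs checking: the article says that no data analysis has been performed, which does not strictly say that no aliquot has been assayed.

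**What to change.** Before any study aliquot is assayed for HIF-1α, confirm from the manufacturer's documentation which specimen the named kit is suitable for. Then make Procedures, Table 6 and the HIF-1α section of the Discussion agree.

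- **If the kit is suitable for EDTA plasma:** state that plasma is the specimen, remove the lysate wording and keep the extracellular-release interpretation. It would help to replace serum with plasma where the stored samples are meant.
- **If the kit needs lysate:** state that HIF-1α cannot be obtained with this kit from the stored plasma of patients already enrolled (34 of 40 at publication). Then either use a HIF-1α immunoassay suitable for plasma, or report HIF-1α as exploratory and outside the Aim 2 conclusion. Starting lysate collection now would reach at most the remaining 6 patients and would not restore the planned comparison.

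The lysate wording should not be deleted before the check. If lysate is in fact required, the deletion would hide the problem.

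**Cost.** In the first case, one enquiry and a few corrected sentences. In the second, a different assay or the downgrading of one of 13 markers. Neither case changes Aim 1, the primary outcome or the other 12 markers.
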